6.3 Situation to discontinue research

Research suspension refers to the clinical research discontinues during process, not ends as planned. The purpose of research suspension is to protect interests of subjects, ensure quality of research and avoid unnecessary economic losses.

(1) If there is serious security problem, the research must discontinue immediately.

(2) If the drug is with poor curative efficacy, or even ineffective, or without clinical significance, the research should discontinue, to avoid delay for effective treatment of subjects or unnecessary economic loss.

(3) If the clinical research program has a major mistake, and is difficult to evaluate drug effects; or a better designed program has significant deviation during implementation, and cannot continue to carry out to evaluate drug efficacy, the research should discontinue.

6.4 Situation to early stop research

The enrollment may end early when target sample size were achieved.

**7. Investigating drugs**

7.1 Name, source of investigational drug

1. Miconazole 10mg mucoadhesive tablet (Tibotec Pharmaceuticals Ltd.，Shenzhen, China)

2. Itraconazole 100mg capsule (Xian Janssen Pharmaceutical Ltd., Xi’an, China)

7.2 Drug inventory and recovery

At each visit, observe doctor should record receive amount, dosage and return amount of drug in detail, to determine the compliance of patient, which should be recorded in case report table.

7.3 Drug preservation

Investigational drug should be locked and kept in safe and controllable indoor areas, and keep dry. Each center should specify a medical management person to keep and manage drugs.

7.4 Drug dispensation and recovery

After passing screening, subjects should be given drugs by researcher in order. At each dispensation, researcher should immediately and accurately fill in drug dispensation record, record amount of dispensed drugs, and remind subjects taking remain drugs back at the next visit; the researcher should recover and check the amount of recovery drugs, which should be recorded in drug dispensation/ recovery record. After research, all remained drugs should be returned to sponsor, and recorded in recovery table of investigational drug.

7.5 Drug inventory and management

At each follow-up, observe doctor should record faithfully and in detail whether the patient takes treatment on time at designated place, to determine the degree of subject compliance. The record should be made at format medical record. Medication compliance=total amount of actual drug use/ total amount of required drug use by program ×100%. At completion, research drug administrator is responsible for giving back remaining drugs to biding unit or destroying remaining drugs. Research drugs should be preserved in locked specific refrigerator in 4 ºC.

**8. Therapeutic Regimen and Research Process**

8.1 Dosage regimen

Trial group: Miconazole 10mg mucoadhesive tablet was administered topically once daily, with the rounded side of the tablet applied to the canine fossa in the morning after brushing the teeth.

| Step 1 | [figure not shown] | Take the patch out from the package. |
| --- | --- | --- |
| Step 2 | [figure not shown] | Moisten the patch with tongue. |
| Step 3 | [figure not shown] | Put the patch on the upper gingiva adjacent to canine with finger. |
| Step 4 | [figure not shown] | Patch is held in place for 30 s with slight pressure. Do not lick with tongue for the first a few minutes to avoid removal. |

Figure 1. Application of miconazole mucoadhesive tablet.

Control group: Itraconazole capsule 100mg once daily, taken immediately after a full meal due to improvement of absorption.

8.2 Administration Instructions

Miconazole mucoadhesive tablet should be applied in the morning, after brushing the teeth. The tablet should be applied with dry hands. The rounded side surface of the tablet should be placed against the upper gum just above the incisor tooth (canine fossa) and held in place with slight pressure over the upper lip for 30 seconds to ensure adhesion. Either side of the tablet can be applied to the gum.

Once applied, miconazole mucoadhesive tablet stays in position and gradually dissolves. Before applying the next tablet, the patient should clear away any remaining tablet material. Food and drink can be taken normally when miconazole mucoadhesive tablet is in place but chewing gum should be avoided.

If miconazole mucoadhesive tablet does not adhere or falls off within the first 6 hours, the same tablet should be repositioned immediately. If the tablet still does not adhere, a new tablet should be placed. If miconazole mucoadhesive tablet is swallowed within the first 6 hours, the patient should drink a glass of water and a new tablet should be applied only once.If miconazole mucoadhesive tablet falls off or is swallowed after it was in place for 6 hours or more, a new tablet should not be applied until the next regularly scheduled dose.

8.3 Research process

Potential participants will undergo preliminary screening for eligibility during visit 1 by investigators, which will include a registered oral medicine specialist. Eligible participants will then undergo initial assessments for review of system (ROS), baseline data collection, which include the symptom scoring, grade of clinical sign of oral candidiasis, measurement of vital signs (temperature, blood pressure and heart rate. ECG), full blood count, kidney function test and liver function test. The candida-related laboratory testing (smear test and fungi culture) will be performed to gather the baseline data of candida infection and colony forming unit count. A daily diary will then be given to record the change of symptoms and occurrence of adverse events and use of topical treatments during the 2-week treatment period. After signing the consent form, participants will be randomly assigned to either the treatment (miconazole mucoadhesive tablet) group or the control (itroconazole capsule) group and the treatment period will start. During this clinic visits, participants will be given 1 weeks’ worth of miconazole mucoadhesive tablet or itroconazole capsules and daily diaries for the fortnight.

In visit 2 of 1week after, the participants will be re-evaluated on the symptom scoring, grade of clinical sign, vital signs, smear test and fungi culture). The participants will repeat 1-week treatment and record the daily diary during the following week. In visit 3 (the following day after the 2-week treatment period) and visit 4 (2-week follow up after treatment ceasing), the participant will be evaluated by performing clinical and laboratory examination as baseline.

Throughout the treatment period, other medication or therapies, such as anti-hypertension drugs, is allowed to be used on an ‘as needed’ basis. During this treatment period, participants will also be required to record their medication intake, including trial interventions, other medications intake and occurrence of adverse events to assist with compliance monitoring and acceptability of intervention. Participants will be asked to return their medication pack to enable the counting of left-overs as well as part of participant adherence monitoring.

[figure not shown]

Figure 2. Outline of trial protocol

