5.2 Secondary outcome measurements

• Clinical improvement rate: (score of symptom and clinical sign at baseline- score of symptom and clinical sign post treatment)/ score of symptom and clinical sign at baseline

• Mycological: Eradication of organism (negative culture and negative microscopy)*

• Safety: Number of patient withdrawals due to adverse reactions; Incidence of adverse reactions (reported as side-effects).

*Candida albicans is found routinely in asymptomatic population, therefore, it would have been inappropriate to use mycological eradication as the primary outcome measure for the study.

The cure is defined as complete clinical response and eradication of Candida spp. at Day 7 or Day 14. A complete clinical response was defined as the complete disappearance of oral candidiasis lesions, and a partial clinical response was defined as ≥60% of clinical improvement rate compared with the score at baseline. <60% of clinical improvement rate and candida persistence, re-infection or species shifts were considered failures. Finally, biologic, local, and general safety was compared between treatments.

Participants will also be required to complete their daily diaries from the start of the treatment period until the end of the treatment period. Blood tests for full blood count and liver and kidney function tests will be conducted at initial assessment and during the final clinic visit (week 4).

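### Smear and culture at visits 2 and 3 may be taken with miconazole product in the mouth; a sampling rule and a visit 4 sensitivity analysis would cheaply remove a possible bias toward the test drug

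*Protocol*

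**What the plan says.** **Timing of samples.** Section 8.3 puts both smear and culture at the one-week visit: "In visit 2 of 1week after, the participants will be re-evaluated on the symptom scoring, grade of clinical sign, vital signs, smear test and fungi". A second treatment week follows. Visit 3 is the day after the two-week treatment period and visit 4 is two weeks after treatment stops; both repeat the laboratory examination done at baseline.

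**Test drug.** Under 8.1 the tablet is "applied to the canine fossa in the morning after brushing the teeth". Section 8.2 adds: "Once applied, miconazole mucoadhesive tablet stays in position and gradually dissolves. Before applying the next tablet, the patient should clear away any remaining tablet material".

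**Comparator.** Section 8.1: "Itraconazole capsule 100mg once daily, taken immediately after a full meal due to improvement of absorption".

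**Use of the readings.** Section 5.2 defines eradication as both culture and microscopy negative, and then says: "The cure is defined as complete clinical response and eradication of Candida spp. at Day 7 or Day 14". It also counts persistence of candida as failure. Section 5.2 places mycology among the secondary outcomes and explains why it should not be primary, although the opening paragraph of section 5 lists the candida elimination rate with the primary measures.

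**Sampling rule.** Nothing in the protocol sets the time of sampling relative to the tablet, or asks for residue to be cleared or the mouth rinsed first.

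**The concern.** Only one arm holds an antifungal product in the mouth. If that product, or drug released from it, enters the specimen, it can suppress growth on the plate. The culture would then partly reflect drug in the sample and not organism removed from the mouth. Such an error adds negatives in the test arm and has no evident counterpart in the control arm. In a comparison analysed for non-inferiority (section 11.2), that pushes toward success.

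The readings exposed to this are the ones that section 5.2 uses for cure. Because either day is enough, one falsely negative reading can satisfy the mycological part of the definition. The visit 4 sample, taken two weeks off drug, is free of the problem, but the cure definition does not use it.

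**Working it through.** **1. Is product in the mouth at sampling?** Section 8.3 dispenses one week's supply at visit 1 and puts visit 2 one week later. Call visit 1 calendar day 0 and visit 2 calendar day 7.

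- First tablet on day 0: seven tablets cover days 0 to 6, so the last is applied the day before visit 2. Residue is possible; a fresh tablet is not.
- First tablet on day 1: seven tablets cover days 1 to 7, so the seventh is due on the morning of visit 2. A tablet may be in place.

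The protocol leaves the start day open. At visit 3 no tablet is due, but 8.2 allows for material remaining up to the next dose, about 24 hours later. So product may be present at either visit, and is certain at neither.

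**2. When would a false-negative culture change the result?** Only if microscopy is also negative. Section 4.1 accepts a diagnosis by smear, culture or both, so the protocol allows the two tests to disagree. In a smear-negative, culture-positive patient, culture alone decides eradication.

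**3. Size per reading.** Apparent gain for miconazole = (1 − p) × s × c, where

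- p = true eradication rate,
- s = share of still-infected patients who are smear-negative,
- c = share of those cultures suppressed by carry-over.

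The documents give none of the three. Assumed ranges: s from 0.3 to 0.5 and c from 0.1 to 0.5. For p, 85% is the only rate in the document, and section 3.2 gives it as itraconazole efficacy, not eradication; 50% to 70% is assumed as a lower range.

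| p | s = 0.3, c = 0.1 | s = 0.5, c = 0.25 | s = 0.5, c = 0.5 |
| --- | --- | --- | --- |
| 85% | 0.45 points | 1.9 | 3.75 |
| 70% | 0.9 | 3.75 | 7.5 |
| 60% | 1.2 | 5.0 | 10.0 |
| 50% | 1.5 | 6.25 | 12.5 |

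For example, 0.15 × 0.3 × 0.1 = 0.0045 and 0.15 × 0.5 × 0.5 = 0.0375. At c = 0 there is no bias.

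These are gains for a single reading. For cure, the either-day rule gives two chances of a false negative. Against that, cure also needs complete disappearance of lesions, so a misread culture matters only in patients already clinically clear. The documents do not allow either effect to be quantified.

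**4. Illustration against a margin.** The protocol states no margin. Section 3.2 gives 85% efficacy, one-sided 5%, 80% power and 158 per group. The formula n = 2 × (1.645 + 0.842)² × 0.85 × 0.15 / d² returns 157.7, rounded up to 158, at d = 0.10 (8 points would need 247 and 12 points 110). A 10-point margin is therefore inferred.

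Suppose miconazole is truly 10 points worse on eradication, with 158 per arm. The chance of passing is Φ(artefact / SE − 1.645), with SE from the unpooled observed rates.

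- 50% v 60%, no artefact: 5.0%.
- 50% v 60%, +2 points: SE = √[(0.52 × 0.48 + 0.60 × 0.40)/158] = 0.0557; Φ(0.359 − 1.645) = 9.9%.
- 50% v 60%, +5 points (s × c = 0.10): SE = 0.0555; Φ(0.900 − 1.645) = 22.8%.
- 75% v 85%, s × c = 0.10, so +2.5 points: SE = 0.0437; Φ(0.572 − 1.645) = 14.2%.

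These show sensitivity only. The rates are assumed, and the margin was inferred from an efficacy assumption and not set for eradication.

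**The case against.** The mechanism is not in the documents. They do not say which site is sampled, give no salivary levels or carry-over data, and do not say whether swallowed itraconazole reaches the mouth. This stands, and it is why the point is put as a risk falling chiefly, not solely, on the miconazole arm.

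A reader might infer that every patient following 8.1 and 8.2 is sampled at visit 2 with a tablet in place. The one-week supply does not support that; it depends on the start day. At visit 3, residue is only conditional.

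The microscopy requirement limits the problem further, as does the lesion requirement for cure. Neither removes it, because smear-negative, clinically clear patients are still decided by culture.

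Section 5.2 treats mycology as secondary, so any effect on the main conclusion runs mostly through the cure definition. That stands too.

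Sampling detail may sit in a laboratory manual, and Figure 2 is not shown. But the tablet instructions and the visit schedule are both written in section 8, and a rule linking them belongs there.

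A reader might also infer that visit 4 should replace Day 7 and Day 14. That would change the question from response at treatment to sustained response. It would also bring in recolonisation, and section 5.2 itself notes that Candida albicans is routine in people without symptoms.

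**Conclusion.** The plan as written permits, but does not establish, a one-sided error toward miconazole in the Day 7 and Day 14 mycology and in the cure that depends on it. The direction is the firmer part, since only one arm retains an antifungal product in the mouth. The size is an assumption: about 0.5 to 4 points per reading at an 85% rate, and about 1 to 12.5 points at 50% to 70%.

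A reader might take the false non-inferiority rates of 10% to 23% as the trial's actual risk. The documents do not support that, because those rates rest on assumed 50% v 60% eradication, an assumed artefact and an inferred margin. Nor do they support saying that eradication is biased. This is a cheap improvement and not a defect that invalidates the design.

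**What to change.** **Section 8.3.** Schedule the visit 2 smear and culture before that day's tablet is in place. At visits 2 and 3, have any remaining tablet material cleared and the mouth rinsed with water before sampling. Apply the same procedure in both arms. Dose and regimen stay as they are.

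**Section 5.2.** Keep the Day 7 and Day 14 results, labelled as on-treatment or end-of-treatment mycology. Add the eradication comparison at visit 4, two weeks off drug, as a pre-specified sensitivity analysis and not as a replacement. If the arms compare similarly at all three times, carry-over is a less likely explanation. If a miconazole advantage fades at visit 4, carry-over and recolonisation are both candidates and the report should say so.

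**Cost.** Wording in two sections and some care over the hour of visit 2. No extra visit or sample is needed, because visit 4 already repeats the laboratory examination. The limitation is that visit 4 includes recolonisation and so may show lower eradication in both arms.

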4.3 Exclusion criteria

1) diagnosis of cryptococcosis or other systemic fungal infections; 2) a history of a known allergy or intolerance to miconazole nitrate and/or itroconazole; 3) use of rifampicin, rifabutin, isoniazid, phenobarbital, phenytoin, methylprednisolone, carbamazepine, terfenadine, astemizole or cisapride; 4) history of pregnancy or breast-feeding; 5) history of psychological disorder that enable to cooperate; 6) hepaticinsufficiency with serum aminotransferase and total bilirubin levels at 1.5 times the upper limit of normal, or active clinical signs 2 months prior to the trial; 7) serum creatinine levels at 1.5 times the upper limit of normal; 8) history of cardiac insufficiency such as ischemic heart failure; 9) history of hematological diseases; 10) use of systemic or topical antifungal therapy within 2 weeks before study entry ( patients received topical treatment with miconazole or nystatin cream or suppositor remain eligible for enrollment in the study); 11) diagnosis of chronic mucocutaneous candidiasis; 12) hyposalivation related disease or drug-taking; 13) HIV positive; 14) history of participating other clinical trials within 4 weeks before study entry.

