**5. Index of efficacy**

All subjects involved were assigned to treatment group receiving 10mg miconazole mucoadhesive tablet for topical use once a day or control group receiving itroconazole capsule 100mg QD for a treatment period of 2 weeks and followed up for 2 week. Primary outcome measures include the evaluation of clinical symptoms (pain and burning sensation rating), signs (pseudomenbran and erythema grade) candida elimination rate. Secondary outcome measures include ameliorative rate of symptoms, occurrence of adverse events and total usage of other therapies as recorded in the participants’ daily diary and laboratory studies which include blood pressure, electrocardiography, full blood count and liver and kidney function tests.

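### Section 8.3 allows other medication as needed during treatment with no exception, so a non-study antifungal, or a drug barred at entry, may be added after randomisation

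*Protocol*

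**What the plan says.** Section 8.3 governs medication during the 2-week treatment period: "Throughout the treatment period, other medication or therapies, such as anti-hypertension drugs, is allowed to be used" as needed. Antihypertensives are given as an example, and no class of drug is excepted.

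Two items in section 4.3 restrict medication, both as criteria for entry. Exclusion 3 is "use of rifampicin, rifabutin, isoniazid, phenobarbital, phenytoin, methylprednisolone, carbamazepine, terfenadine, astemizole or cisapride", with no time window. Exclusion 10 is "use of systemic or topical antifungal therapy within 2 weeks before study entry", with a window that closes at entry and an exemption: "patients received topical treatment with miconazole or nystatin cream or suppositor remain eligible for enrollment in the study".

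After entry, other treatment is recorded. The diary is to "record the change of symptoms and occurrence of adverse events and use of topical treatments during the 2-week treatment period", section 8.3 also asks participants to note other medication taken, and section 5 makes "total usage of other therapies as recorded in the" participants' diary a secondary outcome.

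On outcome, section 5.2 says: "The cure is defined as complete clinical response and eradication of Candida spp. at Day 7 or Day 14". Less than 60% improvement and "candida persistence, re-infection or species shifts were considered failures". Neither definition mentions added antifungal treatment. Under section 11.1 the FAS keeps every randomised patient with at least one evaluation after medication.

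**The concern.** The wording in section 8.3 is a stated permission, not silence. Read literally, it covers a second antifungal given to a patient who is doing poorly at the one-week visit, and it covers any drug on the exclusion 3 list.

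Two things are at stake. First, the trial is a non-inferiority comparison (section 11.2) in which participants, investigators and assessors all know the treatment (section 3.4). If an added antifungal produces the clearance, the cure is credited to the randomised drug. Depending on who adds what, the observed difference can shrink or widen. Second, drugs that the protocol considers unsuitable at entry can be started while the patient is being dosed, and no reason is given for treating the two periods differently. No size can be put on this second part.

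**Working it through.** **Reading the text.** The places where an on-study restriction could stand are these:

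- Section 4.3: exclusion 10 is limited to the 2 weeks before entry. Exclusion 3 has no window but appears only in the list of entry criteria.
- Sections 6 to 6.2 (withdrawal): no drug is named as a reason for withdrawal.
- Sections 8.1 and 8.2 (dosing and application): other drugs are not mentioned.
- Section 8.3: other medication is permitted and recorded.
- Section 11.1: an added antifungal is not named as a ground for leaving any analysis set.

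Figure 2, the trial outline, is not reproduced in the text available and could not be checked. Otherwise nothing bars these drugs after randomisation.

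**Following one patient through.** A patient is still positive at visit 2, adds a non-study antifungal and is clear of lesions and Candida at Day 14. Section 8.3 permits the addition, section 5.2 calls the result a cure, and section 11.1 keeps the patient in the FAS.

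**Reproducing the sample size.** Section 3.2 gives 85% efficacy, one-sided 5%, 80% power and 158 per group, but no margin. A 10-point margin with 85% in both arms gives

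n = (1.645 + 0.842)² × 2 × 0.85 × 0.15 / 0.10² = 157.7, so 158 per group.

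This matches. The 10-point margin is therefore used below, as an assumption.

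**Illustrating the size.** Assume true cure of 75% on miconazole and 85% on itraconazole, which lies exactly on the assumed margin. A share r of failures in an arm adds an antifungal, and a share s of those users is then counted as cured:

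- pT = 0.75 + 0.25 × r_T × s
- pC = 0.85 + 0.15 × r_C × s
- SE = √[pT(1 − pT)/158 + pC(1 − pC)/158]
- P(non-inferiority declared) = Φ[(pT − pC + 0.10)/SE − 1.645]

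The values of r and s are assumptions, since the protocol gives neither. With s = 0.70:

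| Failures who add an antifungal | pT | pC | Difference | P(false non-inferiority) |
|---|---|---|---|---|
| None | 0.7500 | 0.8500 | −0.1000 | 5.0% |
| 10% in both arms | 0.7675 | 0.8605 | −0.0930 | 6.9% |
| 10%, miconazole arm only | 0.7675 | 0.8500 | −0.0825 | 10.6% |
| 10%, itraconazole arm only | 0.7500 | 0.8605 | −0.1105 | 3.0% |

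For the second row, SE = 0.0435 and (−0.0930 + 0.10)/0.0435 = 0.161, so P = Φ(0.161 − 1.645) = Φ(−1.484) = 6.9%.

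With equal use in both arms and s = 0.70, r = 5% gives 5.9% and r = 20% gives 9.5%. With s = 0.30, which allows for additions at visit 2 having about one week to work, r = 5%, 10% and 20% give 5.4%, 5.7% and 6.6%.

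**The case against.** The strongest reply is that the sentence is an ordinary allowance for other illnesses. Its only example treats an unrelated condition, section 8.1 fixes one drug per arm, and section 8.3 has patients simply repeat a second week of the same treatment. That is probably what was meant. But an example does not limit a permission, and a site that applies the sentence as written breaks no rule.

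A second reply is that exclusion 3 carries no time window, while the per-protocol set admits only patients who do not meet an exclusion criterion. On-study use of those drugs might therefore be read as a per-protocol deviation. This is a fair inference and stands as such. It does not reach the FAS, it does not prevent the use, and it does not help with antifungals, because exclusion 10 looks only at the time before entry.

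Three stronger readings are tempting and are not supported:

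- A reader might infer that the permission biases the trial towards non-inferiority. That needs similar use in both arms or more use on miconazole. Use on itraconazole alone lowers the false non-inferiority chance to 3.0%, and 20% use on itraconazole against 10% on miconazole gives 4.2% (s = 0.70). The protocol gives no usage rate, so the sign is open.
- A reader might infer that the protocol is at fault for not stating how the FAS scores a patient who adds an antifungal. Such a rule is commonly left to the statistical analysis plan, which may exist and is not shown. The diary collects data on added treatment during the treatment period.
- A reader might extend the point to the two weeks of follow-up. The permission in section 8.3 covers the treatment period only.

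**Conclusion.** The point holds as a defect in a stated permission. As written, section 8.3 lets a patient add a non-study antifungal and still be a protocol-defined cure in the FAS, and lets a drug barred at entry be started during dosing. Recording and the per-protocol set soften this but do not prevent it.

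Neither the size nor the direction of bias can be established from the protocol. The range of 3.0% to 10.6% against 5.0%, for use by 10% of failures, rests on an assumed margin, assumed true cure rates, an assumed usage rate and an assumed success share. At that rate the users would be few: about 4 of 158 on miconazole (158 × 0.25 × 0.10 = 3.95) and about 2 of 158 on itraconazole (158 × 0.15 × 0.10 = 2.37). The change is worth making because it is cheap and specific, not because a large distortion has been shown.

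**What to change.** Amend section 8.3 to say that, during the 2-week treatment period, other medication is allowed as needed except the drugs listed in exclusion 3 and any non-study systemic or oral topical antifungal. Miconazole or nystatin cream or suppository for non-oral sites remains allowed. This follows the exemption in exclusion 10, although the limit to non-oral sites is added here and is not in the protocol. Any use of a barred drug is recorded as a protocol deviation.

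The cost is one clause. The sample size does not change, and the diary already records other medication and topical treatments. The downside is small: a patient who comes to need a barred drug must stop study treatment or be recorded as a deviation.
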